## Methods

### Study design

The present study follows a hybrid type 1 study design [19], focusing on implementation process factors and outcomes in the context of an effectiveness trial in a prospective quasi-experimental study with control group. A mixed-methods process evaluation among healthcare professionals examines the feasibility and potential barriers and facilitators of ParkinsonAKTIV for routine care, as well as the communication within the regional multidisciplinary Parkinson’s Network Muensterland (PNM+) consisting of medical and non-medical professionals involved in the treatment of patients with PD. For this purpose, quantitative results from a social network analysis and a survey among healthcare professionals will be triangulated with data from qualitative stakeholder interviews and focus group discussions.

Further, the quantitative effectiveness evaluation with two study arms (i.e., intervention arm and observational control arm) examines PD patient’s health-related quality of life and physician-assessed PD patient’s health status (e.g., with the Unified Parkinson Disease Rating Scale (UPDRS)). Moreover, a health economic evaluation of the ParkinsonAKTIV intervention is conducted using patient-reported outcomes and routine data from a German statutory health insurance.

The study observation period is set to 12 months, and data for the effectiveness evaluation and the associated health economic evaluation will be collected at five timepoints, as shown in Table 1.

**Table 1 Tab1:** Trial flow-chart according to SPIRIT guidelines with schedule of enrollment, intervention, and assessment

Timepoint	Study period					
	Preceding study	Enrolment/allocation	Post-allocation			Close-out
	− *t*_1 (12 months prior)_	0	*t*_1_	*t*_2_	*t*_3_	*t*_4 (12 months)_
*Enrolment*						
Eligibility screen		X				
Informed consent		X				
Allocation		X				
*Interventions*						
ParkinsonAKTIV						
Control Group (treatment as usual)						
*Assessments*						
Demographic aspects		X				
PDQ-39		X		X^a^		X
FIMA		X		X^a^		X
Schwab & England—activities of daily living scale		X^a^	X^a^	X^a^	X^a^	X^a^
UPDRS		X^a^	X^a^	X^a^	X^a^	X^a^
Hoehn & Yahr scale		X^a^	X^a^	X^a^	X^a^	X^a^
Routine data	X	X	X	X	X	X

PDQ-39 Assessment of patient-reported health-related quality of life with the Parkinson’s Disease Questionnaire. *FIMA* assessment of patient-reported healthcare costs. *UPDRS* assessment of patient’s PD-related status through neurologists

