### Effectiveness evaluation

*Recruitment of intervention group* Recruitment of PwP takes place during face-to-face consultations by their treating neurologists where further information about ParkinsonAKTIV is provided. Until the caseload is reached, all new patients that fulfil the inclusion criteria, will be enrolled into the intervention arm. Additional information about the procedure for participation is available on the PNM+ website as well as flyers.

*Recruitment of control group* To compare the treatment of PwP in ParkinsonAKTIV with standard care, members of a nationwide support group for PD, the Deutsche Parkinson Vereinigung e. V. (dPV), are approached for study participation through their member’s journal. The dPV member pool will be approached twice for participation in the survey, once for the baseline survey and once at the end of the study.

Patients eligible for the intervention arm must fulfill the following inclusion and exclusion criteria:

*Inclusion criteria*
Primary PD according to the international classification (ICD 10 G20.x)Age of ≥ 30 yearsExisting medical treatmentPD care must be fully provided in the region Muensterland, Tecklenburger Land and the district and city of Osnabrueck

*Exclusion criteria*
Secondary PDInsufficient knowledge of the German languageIntellectually and linguistically unable to answer the questionnaires

*Data collection* For the effectiveness evaluation and the health economic evaluation, quantitative data will be collected via paper–pencil surveys among PD patients (i.e., primary outcome: health-related quality of life and secondary outcomes: patient-reported healthcare costs, see Table 1). In addition, neurologists assess disease specific measures during their face-to-face consultations (i.e., secondary outcomes: disease severity and PD symptom severity, see Table 1).

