The severity of PD and activities of daily living will be assessed using the PD-specific Schwab and England Activities of Daily Living scale [14] by the treating neurologist. This scale rates the functional status of patients with PD on a scale from 0, indicating worst possible function, to 100, indicating no impairment.

Healthcare service utilization will be measured using the generic Questionnaire for Health-Related Resource Use in an Elderly Population (FIMA) [15]. It contains 28 questions that consider the patients’ utilization and healthcare costs of outpatient and inpatient treatments, medications, and other treatment procedures, such as physical therapy.

*Health economic evaluation* The health economic evaluation will be performed as a cost-effectiveness analysis considering total costs (direct and indirect costs) collected from patients via FIMA and quality of life as effect measures collected via PDQ-39. In addition, a cost analysis from a payer’s perspective will be performed using routine data from a statutory health insurance.

*Data analysis* Descriptive and associated analyses will be conducted to determine sample characteristics and provide summaries of outcome measures.

The primary and secondary outcomes will be evaluated according to the intention-to-treat principle. To test the robustness of the data, per-protocol analysis with complete cases only will be performed.

For the analysis of the primary outcome measure, PD-specific quality of life, all 39 items will be grouped into eight index scores, which then represent a percentage value between 0 and 100 (100 = many health problems). In a next step, linear models will be used to examine the difference in primary outcome between groups and will be reported as gain in quality of life within the 12-monthts observation period, with a 95% confidence interval. Sensitivity analyses will be conducted using multiple regression analysis, considering covariates such as age, gender, or duration of PD.

Secondary outcomes will be analyzed with dependent t-tests, to compare for potential differences in the intervention group within the course of the study (12 months).

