Cost-effectiveness will be analyzed using an incremental cost-effectiveness ratio (ICER). The ICER measures the additional cost per unit of health gain and compares the differences between the intervention arm (specified as ‘i’ in the formula) and control arm (specified as ‘c’ in the formula) in terms of the mean total costs in the numerator and mean effects in the denominator:$${\text{ICER}} = {{\left( {{\text{costs}}_{{\text{i}}} - {\text{costs}}_{{\text{c}}} } \right)} \mathord{\left/ {\vphantom {{\left( {{\text{costs}}_{{\text{i}}} - {\text{costs}}_{{\text{i}}} } \right)} {\left( {{\text{effects}}_{{\text{i}}} - {\text{effects}}_{{\text{i}}} } \right)}}} \right. \kern-0pt} {\left( {{\text{effects}}_{{\text{i}}} - {\text{effects}}_{{\text{c}}} } \right)}}$$

To address uncertainties in the cost-effectiveness analysis, cost-effectiveness planes will be plotted based on a non-parametric bootstrapping method with 5.000 bootstrap replications. Furthermore, a cost-effectiveness acceptability curve (CEAC) will be constructed and univariate sensitivity analyses will be performed.

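### The ICER takes incremental cost as a plain difference in mean FIMA totals between non-randomised arms and does not use the baseline FIMA cost scheduled in both

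*Protocol article*

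**What the plan says.** All references are to the protocol article.

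- **Estimator.** The Data analysis part of the section Effectiveness evaluation gives the ICER as a formula, intervention minus control, "in terms of the mean total costs in the numerator and mean effects in the denominator". Uncertainty is shown by a non-parametric bootstrap with 5,000 replicates, a cost-effectiveness plane, an acceptability curve (CEAC) and univariate sensitivity analyses. No baseline cost term appears in any of these.
- **Design.** Study design calls this a "prospective quasi-experimental study with control group". Intervention patients are enrolled by their treating neurologists in one region. Controls are "members of a nationwide support group for PD", invited through the group's journal.
- **Timing of FIMA.** Table 1 schedules FIMA at time 0 and at 12 months in both arms; only the t2 assessment is marked as intervention-only. The control pool is approached twice, "once for the baseline survey and once at the end of the study".
- **Related analyses.** The PDQ-39 group difference "will be reported as gain in quality of life within the 12-monthts observation period". The Data collection paragraph lists FIMA costs among the "secondary outcomes: patient-reported healthcare costs", and the analysis rule for that class is: "Secondary outcomes will be analyzed with dependent t-tests, to compare for potential differences in the intervention group within the course of the study".
- **Possible safeguards.** The sample size paragraph mentions 1:1 matching without naming its variables. Regression on age, gender or disease duration is a sensitivity analysis, described in the paragraph on the primary outcome.

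**The concern.** Under randomisation, a difference in mean follow-up cost estimates the incremental cost without bias. Here the arms come from different sources, and members of a nationwide patient association who answer a journal invitation may well have used services differently before the study from patients enrolled in regional neurology practices. Where that difference carries on into follow-up, the formula attributes it to ParkinsonAKTIV.

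None of the stated procedures clearly prevents this. The covariate regression concerns the PDQ-39 and does not name baseline cost. The matching may help, but its variables are not given. The paired tests use the intervention arm only and so offer no control between arms. The bootstrap resamples the same two groups, so every replicate is centred on the same shifted cost difference; the plane and CEAC would show sampling uncertainty around it and no sign of the shift. Effects on healthcare costs are part of the study's stated second aim, so this is a main result.

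**Working it through.** **Inputs.** From the sample size paragraph: 176 per group, d = 0.3, two-sided alpha 0.05, power 0.80. From Table 1: FIMA at time 0 and 12 months in both arms. The article gives no mean cost, cost SD or ICER, so the work below is in SD units of cost, and B, p and r are assumptions:

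- B = baseline cost gap between arms that remains after any matching, 0.1 to 0.3 SD;
- p = share of that gap that persists into 12-month cost, 0.3 to 1.0;
- r = within-arm correlation of baseline and 12-month cost (equal SDs assumed, so r is also the regression slope), 0.4 to 0.8.

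**Step 1: the plan's own figure.** For d = 0.3 the normal approximation gives 175 per group. The exact t-test gives 175.38, so 176, with power 0.801. The stated 176 is reproduced and serves here only to set the standard error.

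**Step 2: standard error of the plain contrast.** sqrt(2/176) = 0.107 SD.

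**Step 3: shift in the numerator.** Expected numerator = true incremental cost + p × B. The last column is the chance, with no true cost effect, that a two-sided 5% test finds a difference in the direction of the gap (2.5% with no gap; normal approximation).

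| B (SD) | p | Shift p × B (SD) | Shift / SE | Chance of a spurious difference |
|---|---|---|---|---|
| 0.1 | 0.3 | 0.03 | 0.3 | 5% |
| 0.1 | 1.0 | 0.10 | 0.9 | 15% |
| 0.2 | 0.5 | 0.10 | 0.9 | 15% |
| 0.2 | 1.0 | 0.20 | 1.9 | 47% |
| 0.3 | 0.3 | 0.09 | 0.8 | 13% |
| 0.3 | 0.7 | 0.21 | 2.0 | 50% |
| 0.3 | 1.0 | 0.30 | 2.8 | 80% |

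The shift therefore runs from 0.3 × 0.1 = 0.03 SD to 1.0 × 0.3 = 0.30 SD. If B = 0 or p = 0 there is none.

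**Step 4: what each adjustment leaves.**

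- Plain difference: p × B.
- Regression on baseline cost: (p − r) × B, with SE 0.107 × sqrt(1 − r²) = 0.098, 0.085 and 0.064 SD at r = 0.4, 0.6 and 0.8.
- Difference in change from baseline: (p − 1) × B.

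At B = 0.3 and p = 0.3 the plain difference is off by +0.09 SD and the change score by (0.3 − 1) × 0.3 = −0.21 SD, a larger error of opposite sign. At p = 1 the change score is unbiased, while regression leaves (1 − r) of the gap: 60%, 40% or 20% at the three correlations. Since r lies between 0 and 1, the regression bias always lies between the other two, and it vanishes when p = r. Change scores beat the plain difference on bias only when p exceeds 0.5.

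**Step 5: effect on the ratio, illustration only.** Assume a true incremental cost of 500 currency units and a gain of 3 PDQ-39 points: ICER = 500/3 = 166.7. With B = +1000 and p = 0.7 it becomes (500 + 700)/3 = 400.0. With B = −1000 and p = 0.7 it becomes (500 − 700)/3 = −66.7. The sign can change.

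**The case against.** The strongest reply is that the article prints the generic ICER formula, treats costs and effects in parallel, and nowhere rules out adjustment. A condensed article may leave the matching variables, and any regression of costs inside the bootstrap, to a fuller document. This stands in part: the formula does not prove that no adjustment will be made, and matching could remove some or all of the gap. Even so, the article does fix an estimator, and as fixed it has no baseline term in a design that needs one.

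It is also fair to say that no cost figures exist, so no size can be established, and that only the persisting share of a gap carries over. Both stand, and the range above reflects them. Nor is it stated that the two control surveys are linked for each person, so the adjustment may be harder than Table 1 suggests.

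Two stronger readings are tempting, and the document does not support them. A reader might infer that cost and effect are defined inconsistently, because the PDQ-39 is reported as a gain and cost as a total. Cost accrues over a period while quality of life is a state, so dividing incremental cost by health gain is ordinary practice. A reader might also infer that the paired test of FIMA cost contradicts the ICER. That test covers the intervention arm alone and asks about change within it, which is a different question from the contrast between arms.

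**Conclusion.** The point holds as one of analysis choice. The stated incremental cost is open to confounding by pre-study cost, and a planned baseline measurement that could reduce this is not used. It concerns the cost numerator, the plane and the CEAC, not the PDQ-39 model.

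Under the assumed gap and persistence, the shift is about 0.03 to 0.30 SD, that is 0.3 to 2.8 standard errors with 176 per arm. It is negligible at the lower end and decisive at the upper end. The assumptions are that some gap remains after matching and that part of it persists; the document settles neither. It would be too strong to say that every pre-existing cost difference passes in full into the ICER, because that needs full persistence and no help from the matching. The change should be made, since it costs little and the article offers no other clear protection for costs.

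**What to change.** Estimate incremental cost by regressing 12-month FIMA cost on arm and baseline FIMA cost. Resample patients (or matched pairs, if the matching is kept), and in each of the 5,000 replicates re-estimate this cost difference together with the PDQ-39 effect, so that the plane and CEAC rest on the adjusted pair. Report the difference in change from baseline as a sensitivity analysis rather than the main one, because it over-corrects if the gap persists only partly. State that baseline FIMA cost is a covariate and is not added into total costs. Name the matching variables and say whether baseline cost is among them.

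The cost is some wording and a few lines of code, with no added assessment, provided that the control arm's two surveys can be linked for each patient; this should be confirmed. Patients without a linked baseline FIMA need imputation. Regression will leave some residual bias whenever the persisting share of the gap differs from the baseline-to-follow-up slope, and the report should say so.

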## Perspective

To the best of our knowledge, this is the first study testing and evaluating the implementation of a multidisciplinary treatment coordination platform for PwP in Germany. The ParkinsonAKTIV study aims to test a multidisciplinary, digitalized approach called JamesAKTIV, including a wide range of healthcare professionals intimately involved in the community-based care for PwP. It is anticipated that ParkinsonAKTIV can overcome current barriers to communication and coordination within PwPs’ care paths with special regard to non-pharmacological therapies. The German PD care landscape is characterized by a fragmented system with different healthcare professionals caring for PwP, hence prescribing PD treatment to patients yet not communicating with each other about the respective patient. The multidisciplinary communication and coordination platform JamesAKTIV is designed to address communication barriers by using digitalized quickcards as means of communication about PwPs' treatment.

An outstanding strength of ParkinsonAKTIV is its study design. Combining quantitative and qualitative data collection through a process evaluation and an effectiveness evaluation, gaining deeper insights into patient’s quality of life and ParkinsonAKTIV’s cost-effectiveness. Specifically, during process evaluation, a social network analysis will be conducted which is, to our knowledge, a novelty in analyzing teamwork in multidisciplinary PD healthcare teams.

It is assumed that the results of this study will further strengthen ParkinsonAKTIV. First, the findings are expected to provide evidence of an increase in quality of life of PwP, less severe PD symptoms, and a better ability to participate in activities of daily living. Second, ParkinsonAKTIV has high potential of increasing PwPs’ quality of care through sufficient and more tailored prescription of non-pharmacological therapies. Third, improved communication among health professionals could lead to an increased patient safety.

## Data Availability

The data will be deposited on a protected server of the Institute for Applied Health Services Research (inav GmbH). Access is strongly regulated even for study personnel. Owing to the difficulty of de-identification (routine care, qualitative data, etc.), individual participant data will not be shared publicly. Upon reasonable request that includes a methodologically sound proposal for the usage of data that is also approved by the responsible review committee data may be shared.

## Abbreviations

CEAC: Cost-effectiveness acceptability curve
dPV: Deutsche Parkinson Vereinigung e. V.
FIMA: Generic Questionnaire for Health-Related Resource Use in an Elderly Population
ICD-10: International Classification of Disease, Tenth Revision
ICER: Incremental cost-effectiveness ratio
PD: Parkinson’s Disease
PDQ-39: Parkinson’s Disease Questionnaire
PNM+: Parkinson’s Network Münsterland
PNO+: Parkinson’s Network Osnabrueck
PwP: Patients with Parkinson’s Disease
UPDRS: Unified Parkinson’s Disease Rating Scale
